### Sensitisation and recruitment

Key stakeholders will be involved in the study and its design. Prior to implementation, meetings will be held with the NTDP, and at each study site, where key stakeholders (chiefs, community leaders and study participants) will be sensitised about the study objectives, interventions, evaluation procedures, and requested to provide input as well as the need for their participation in the study. Community meetings will be held to describe the purpose of the study, the interventions, the evaluation procedures to be followed, and the risks and benefits associated with participation. Individuals will have the opportunity to ask questions for which answers will be provided by the research team.

Consent for the intervention will be provided at the community level with the option for individuals to opt out. Community drug distributors (CDDs) used by the NTDP will number all houses and update their community registers through coordination with the chiefs and village elders. Using a random number generator in Excel, households will be selected until the sample size for each village is attained. Subsequently, households selected for inclusion into the study will be visited by field staff, for consenting and recruitment into the study. In each household visited, written informed consent to conduct the household-level questionnaire will be sought from the household head. Individual-level consent will be sought from selected individuals, 18 years old and above (either for themselves or their children) and written assent sought from children aged 12–17 years.

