### Sample size calculation

The sample size was calculated based on the null and alternative hypotheses, together with the type-I and type-II errors defined as follows:

Null hypothesis (H_0_): the additional dose of IVM is not more effective than the standard single dose per annum treatment (i.e. Treatment – Control = 0).

Alternative hypothesis (H_A_): the additional dose of IVM is more effective than the standard dose (i.e. Treatment − Control > 0).

The type-1 error rate (*α*), i.e. rejecting H_0_ when it is true, is set at 0.05, with a two-sided test. To control for type-II error (*β*), the probability of rejecting H_0_ when it is false is set at 0.80, taking into consideration budget allocation.

The hotspot districts have been receiving an annual single dose of IVM for the past 15 years with the prevalence rates ranging between 1% and 18.2%. Therefore, it is assumed that the new intervention would have an effect, expected to be larger than the effect of the standard control approach, with an effect size of 0.4. Based on these assumptions, the sample size was calculated using the Optimal Design software [34]. Thus, for 0.80 power the study requires a cluster size of 58.

With an expected non-response and a loss to follow-up of 37% (determined from previous unpublished studies), the sample size per cluster has been determined to be 80. With 18 clusters to be surveyed, a total of 1440 study participants, from the two study districts, will be expected to take part in this trial.

Study participants will not be paid as part of the survey. However, in order to mitigate the high dropout rates during follow-ups, participants will be compensated for the time lost for working during the days they are participating in survey activities, with an amount of 7 Cedis (equivalent to US$1.61). They will also be contacted at 14 days and 7 days prior to follow-up, in order to ensure their availability. Even though there is always the possibility of emergencies and other social responsibilities that may result in their unavailability, efforts will be made to reach them.

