### Cluster randomisation

Randomisation will be stratified by the prevalence of LF (as determined in the baseline surveys). The randomisation sequence generation will be undertaken by an independent statistician using computerised random-number generation. Sealed envelopes containing cluster identification will be placed in pre-stratified ballot boxes, with community leaders invited to select envelopes from the boxes and directed to put the selected envelope in a box labelled A or B (corresponding to the two study groups, each with nine clusters) according to the pre-generated randomisation sequence for that stratum. With an average household size of six and the frequency of under 5 years being 14.3%, 45 households will be randomly selected in each cluster and five eligible household members recruited into the cross-sectional surveys. Owing to the nature of the interventions, participants will not be blinded to their group randomisation. However, the identity of the study groups will remain hidden until the completion of community sensitisation and randomisation in order to eliminate participation bias. Further, the laboratory technicians conducting the parasitological examinations and the statistician responsible for analysis will be blinded to the group assignment. The blinding to the laboratory technicians and statistician will be done using sample/study participant identification codes for samples and results which will not be linked to the study groups.

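### Five people from each of 45 households makes 225 per village, not 80; if 80 governs, sampling about 16 whole households costs modest, avoidable precision and leaves the 0.80 power not assured

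*Protocol article*

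**What the plan says.** The sample size section of the protocol article states that "for 0.80 power the study requires a cluster size of 58". It raises this to 80 per cluster for an expected 37% non-response and loss, and multiplies by 18 clusters to reach 1440. The trial registration table (Table 2) repeats 1440 as the target.

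The section on sensitisation and recruitment says that "households will be selected until the sample size for each village is attained". The section on cluster randomisation gives a different rule: "45 households will be randomly selected in each cluster and five eligible household members recruited into the cross-sectional surveys". It derives this from an average household of six with 14.3% under five years, so 6 x (1 - 0.143) = 5.1 members are eligible by age. Five per household is therefore close to the whole eligible household.

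The printed sample size calculation gives no intracluster correlation at village level and none at household level. The analysis sections mention repeated measures per individual and clustering within groups and within subjects, but do not name the household as a level.

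**The concern.** There are two linked problems. First, the sampling rule and the sample size disagree by a factor of 225/80 = 2.8, and field staff cannot follow both.

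Second, if the target of 80 governs, five per household fills a village sample from 80/5 = 16 households. Members of one household share several things that the protocol itself treats as relevant to infection: nets and barriers are recorded per house, net use and past MDA participation are named adjustment covariates, and treatment is delivered house to house. Infection status is then likely to be correlated within households beyond the village effect, so each extra member adds less information than a person from another household. At stake is the precision of each village prevalence, and through it the stated power. The same 80 people could be drawn from the 45 households that the randomisation section already selects.

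**Working it through.** **Inputs from the protocol article.** Type I error "is set at 0.05, with a two-sided test"; the calculation proceeds "with an effect size of 0.4" (scale not given, taken here as a standardised difference); two groups, "each with nine clusters", so J = 18; 58 complete per village for power 0.80. The article says that "the sample size was calculated using the Optimal Design software" but prints no correlation.

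**Assumed.** Village correlation r (back-solved below) and household correlation h = 0.05 / 0.1 / 0.2 / 0.3.

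**Formula.** Variance of a village mean, in units of the total variance: V = r + (1 - r) x [1 + (k - 1)h]/n, with n people per village and k per household. Power comes from the noncentral F(1, 16) with lambda = J x 0.4² / (4V) = 0.72/V.

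**Step 1: the plan's own figure.** Without r, the 0.80 cannot be checked directly. With no household term and n = 58, power is 0.80 when r = 0.0647: V = 0.0647 + 0.9353/58 = 0.0808 and lambda = 8.91. With r = 0.05 power would be 0.871, and with r = 0.10 it would be 0.650. Ignoring clustering altogether, an effect of 0.4 needs only about 99 per arm (11 per village), so some village correlation was probably used.

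**Step 2: the two sampling rules.** 45 x 5 = 225 per village and 225 x 18 = 4050 in total, against 80 and 80 x 18 = 1440. At five each, 80 people need 16 households; over 45 households, 80/45 = 1.8 each.

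**Step 3: 58 completers, r = 0.0647, taken as evenly spread over the households.** From 16 households k = 58/16 = 3.6; from 45 households k = 58/45 = 1.3.

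| h | 16 households: design effect | worth | power | 45 households: design effect | worth | power |
|---|---|---|---|---|---|---|
| 0.05 | 1.13 | 51 | 0.790 | 1.01 | 57 | 0.799 |
| 0.1 | 1.26 | 46 | 0.780 | 1.03 | 56 | 0.798 |
| 0.2 | 1.53 | 38 | 0.760 | 1.06 | 55 | 0.796 |
| 0.3 | 1.79 | 32 | 0.741 | 1.09 | 53 | 0.793 |

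Worth means n divided by the design effect. Losses will not fall evenly. If every completer under the wider spread still had a household partner in the sample (k = 2), power would be 0.796 / 0.792 / 0.785 / 0.777, still above the 16-household figures.

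**Step 4: the literal reading, 225 per village at k = 5.** Power is 0.855 / 0.850 / 0.842 / 0.834. After 37% loss (142 left, still counted as five each) it is 0.840 / 0.834 / 0.821 / 0.808.

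**Step 5: sensitivity to r at h = 0.2, 58 completers.** With r = 0.05, power is 0.829 from 16 households and 0.866 from 45. With r = 0.08 it is 0.695 and 0.726. The direction does not change; whether power is above or below 0.80 does.

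**The case against.** A reader might infer that the stated 0.80 power is definitely not delivered. The documents do not support that, for four reasons.

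- Neither correlation is given. The village value is back-solved to give exactly 0.80, so any added variance must fall below 0.80 by construction. At r = 0.05 the 16-household design still exceeds 0.80 for every h examined (0.808 at h = 0.3).
- Read literally, the randomisation section gives 225 per village, and power stays above 0.80 throughout the range examined. At r = 0.0647 the effective number at full response would fall below 58 only if h exceeded (225/58 - 1)/4 = 0.72.
- It would be wrong to say that the effective number is below 58 even with full response. Full response means 80 people, and 80/(1 + 4h) is below 58 only if h exceeds (80/58 - 1)/4 = 0.095.
- Combining 58 completers with five per household (power 0.785 / 0.769 / 0.740 / 0.711) overstates the loss. It would apply only if whole households dropped out; 58 from 16 households is 3.6 each.

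It can also be said that a journal article condenses the protocol and that unprinted software inputs are no defect. That is fair: the absence of a household term is read from the printed calculation and cannot be confirmed. Recruitment had also started, so a change is more than editing.

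Two things stand. The sections contradict each other on the number per village. And for any positive household correlation, 80 people from 16 households carry less information than 80 people from 45.

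**Conclusion.** The contradiction is certain and needs no assumption: 225 per village (4050 in total) against 80 (1440), with a stopping rule that fits only the latter.

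The precision point is conditional. If 80 governs, r is about 0.065 and h lies between 0.05 and 0.3, power is about 0.79 to 0.74 from 16 households against about 0.80 to 0.79 from 45. That is a loss of roughly 1 to 5 percentage points from the wider spread. It is modest because between-village variance dominates: at this r, even unlimited people per village would give only 0.88. The 0.80 is not assured; the documents do not show that it is missed.

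**What to change.** Reconcile the recruitment, sample size and randomisation sections. In the randomisation section, replace the instruction to recruit five members with one or two randomly chosen eligible members from each of the 45 households until 80 are reached (for example, two from 35 households and one from 10: 70 + 10 = 80). In the sample size section, state the village correlation and an assumed household correlation, and restate power with the design effect 1 + (k - 1) x household correlation. If 225 per village is what the sponsor intends, the 80 and the 1440 must be corrected instead.

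The number of blood samples stays at the target of 80 per village. The cost is 45 household visits per village and not 16, although 45 are already planned, and a random choice within each household. Recruitment began on 19 May 2017, so the change needs an amendment filed with the ethics committees, and villages already sampled under the five-member rule should be identified.

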### Entomologic surveillance

Surveys for vectors and transmission of LF will be carried out quarterly throughout the first year, and subsequently every 6 months. Vector collection will be carried out in selected villages. To ensure that mosquitoes do not cross over between communities, vector collection communities will be at least 2 km apart.

In each community collections will be undertaken in 10 selected participants’ households, distributed so as to be representative of the community. The community will be divided into four approximate sections. All households in the section will be numbered. The day before the planned collection, the dice will be rolled to select the households. For example, if the dice is rolled and the number is 5, then the fifth house will be selected. Upon selection, the household head will be approached, the study explained and consent sought. If a household refuses participation or household members are absent, a different household will be selected as a replacement. Subsequently, the sum of the dice rolls will be added to the previous number, for the selection of the remaining households. At least two households will be selected per section.

Collections will be undertaken using the Pyrethrum Spray Collection (PSC) in the rooms provided by the consenting individuals. The PSC will be undertaken in the morning from 5 a.m. to 8 a.m. White bed sheets will be laid on the floor and other surfaces in the rooms, after mosquito hiding places (under the bed, tables) have been disturbed to displace any resting mosquitoes. The room will then be sprayed with pyrethrum insecticide (RAID insecticide), commonly found on the Ghanaian market) and left for about 15 min, after which the white sheets will be inspected for any dead or knocked down mosquitoes. The mosquitoes will be collected and placed in a petri-dish labelled with the village name, GPS coordinates and collection date. Collected mosquitoes will be identified using morphological identification keys [36, 37]. All mosquito collections will be undertaken by trained entomologists at the NMIMR.

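### The cumulative dice rule for mosquito-collection households gives unequal selection chances and caps the reachable house number whatever the section size, so it does not by itself deliver a representative sample

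*Protocol article*

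**What the plan says.** The rule is in the Entomologic surveillance section of the Protocol article.

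- Number of households: "In each community collections will be undertaken in 10 selected" participants' households, to be "distributed so as to be representative of the community".
- Spread: "The community will be divided into four approximate sections", and "At least two households will be selected per section".
- List: "All households in the section will be numbered".
- First house: "For example, if the dice is rolled and the number is 5, then the fifth house will be selected".
- Later houses: "Subsequently, the sum of the dice rolls will be added to the previous number, for the selection of the remaining households".
- Refusals and absences: a different household is taken. How it is chosen is not said.

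The printed rule does not scale the step to the section size, start at a random point on the whole list, or return to the top of the list. The article does not give the number of houses per section, the order of numbering or the number of dice.

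For the human surveys the same article uses another method (Sensitisation and recruitment): "Using a random number generator in Excel, households will be selected until the sample size for each village is attained".

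**The concern.** A rule that starts at the top of a numbered list and moves down by dice totals stops at a point fixed by the dice. Houses beyond that point have no chance of selection, and houses before it have unequal chances. Neither fits the stated aim of representing the community.

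The entomological indices are not incidental. The study objectives include the effect of treatment on entomological transmission indices, and the Background presents assessment in vectors as something that earlier trials lacked. Mosquito infection rates and transmission potential will be calculated from the households chosen this way. Weights could in principle correct for unequal chances that are known and above zero. No analysis can correct for houses that could never be chosen.

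**Working it through.** The plan gives no figure of its own on this point, so there is none to reproduce. The inputs are the ten households, four sections, minimum of two per section and dice rule set out above. The number of dice, and whether the sum is a fresh roll or a running total, are not stated, so three readings are taken. Section size N is not stated; 25 and 50 are assumptions for illustration.

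**1. Picks per section.** 4 × 2 = 8, which leaves 10 − 8 = 2 to place. The split is 3+3+2+2 or 4+2+2+2. Either way at least two sections have exactly two picks.

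**2. Highest reachable house.** Let r be one roll of one die (1 to 6).

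- (a) One die, each new roll added: house k = r1 + … + rk, so the maximum is 6k.
- (b) One die, running total of rolls added to the previous number: second house = 2·r1 + r2, third = 3·r1 + 2·r2 + r3.
- (c) Two dice, each sum added: the maximum is 12k, and house 1 can never be chosen.

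| Reading | Two picks | Three picks |
|---|---|---|
| (a) | 12 | 18 |
| (b) | 18 | 36 |
| (c) | 24 | 36 |

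Four picks in one section would raise the cap under (a) to 24. None of these caps depends on N.

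**3. Selection chances within reach, reading (a).**

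- Two picks, house 6: P(first = 6) + P(sum of two = 6) = 6/36 + 5/36 = 11/36 = 0.306.
- Two picks, house 12: 1/36 = 0.028, so the ratio is 11 to 1.
- Three picks, house 6: 36/216 + 30/216 + 10/216 = 76/216 = 0.352. House 18: 1/216 = 0.005.

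In a 12-house section with two picks every house is reachable, and an equal chance would be 2/12 = 0.167 for each. The rule gives 0.028 to 0.306.

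The mean house number picked is (3.5 + 7)/2 = 5.25 with two picks and (3.5 + 7 + 10.5)/3 = 7.0 with three. The share of picks among houses 1 to 10 is (1 + 33/36)/2 = 96% with two picks and (1 + 33/36 + 1/2)/3 = 81% with three.

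**4. Share of houses with no chance.** This is (N − cap)/N, with house 1 also lost under (c).

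| Reading, picks | N = 25 (assumed) | N = 50 (assumed) |
|---|---|---|
| (a), two | 13/25 = 52% | 38/50 = 76% |
| (a), three | 7/25 = 28% | 32/50 = 64% |
| (b), two | 7/25 = 28% | 32/50 = 64% |
| (b), three | 0% | 14/50 = 28% |
| (c), two | 2/25 = 8% | 27/50 = 54% |
| (c), three | 1/25 = 4% | 15/50 = 30% |

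**5. Where exclusion starts.** Under (a), a section with two picks loses houses once N exceeds 12, which is 4 × 12 = 48 per village if sections are equal. The Cluster randomisation section has 45 households randomly selected per cluster. On that figure a village has at least 45, or 45/4 = about 11 per section. For the same two-pick sections the start is above 4 × 18 = 72 houses per village under (b). Under (c) the upper cap bites above 4 × 24 = 96.

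**6. Short lists.** At 11 houses under (a), every house is reachable, but a pick can run past the end: on average 1/36 = 0.03 of two picks, or 1/36 + 81/216 = 0.40 of three. The printed rule does not cover this.

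**The case against.** The strongest reply is that exclusion is conditional. No section or village size is given, and at about 11 houses per section nothing is out of reach with one die. With three picks, readings (b) and (c) exclude only 0% to 4% at 25 houses. This stands: the share excluded cannot be stated as a fact about this trial.

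The frame is also ambiguous. The article speaks of participants' households, which could mean only the enrolled ones. Those would already be a random draw and short enough to be reachable with one die. Against this, all households in the section are to be numbered and the household head is approached for fresh consent, which favours the wider frame. The text does not settle it. On the narrow frame the unequal chances remain, and so does the problem of running off the list.

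A reader might infer that mosquitoes will come from one fixed corner of each section. The documents do not support that. They give neither the order nor the starting point of numbering, so a low number implies no location. The dice are rolled the day before each collection, so houses can change between rounds within the reachable range. The four sections, with at least two houses each, also give real geographic spread.

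A reader might also infer a biased comparison between arms. That is not shown: the printed rule makes no distinction between arms, and the primary outcome is LF prevalence in people.

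Finally, this is a condensed article, and the standard operating procedures it promises may fix the number of dice or the numbering. That may narrow the readings. It does not change the rule as printed, which is specific enough to follow and gives unequal chances when followed.

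**Conclusion.** The point holds in a limited form. On all three readings the dice rule gives unequal chances and a cap that ignores section size: 12 or 18 with one die and each roll added, 18 to 36 otherwise, for two or three picks. The 11-to-1 contrast between houses 6 and 12 needs no assumption about section size beyond both houses being on the list, but it does assume one die and two picks.

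How many houses have no chance depends on sizes that the article does not give; the percentages at 25 and 50 houses are illustrations. The rule therefore does not by itself deliver the representativeness claimed for the entomological indices. Geographic clustering, error in any particular index and bias between arms are not established. The change is worth making because it is simple and the indices serve a stated objective.

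**What to change.** 1. State the frame: all households in the section, or only those enrolled in the survey.
2. Replace the dice rule with an equal-probability draw of two or three house numbers per section from the full numbered list, using the Excel random-number generator already planned for survey households. Each house in a section of N then has chance k/N, for example 2/25 = 0.08 or 3/25 = 0.12 at an assumed 25 houses, and none has zero.
3. Draw at random which two sections receive three households, and record N for each section so that the selection chances are known.
4. Draw a randomly ordered reserve list at the same time and use it in order for refusals and absences.

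The cost is close to nil. The section lists have to be made under the present rule anyway, and the generator is already in use. No change to the number of households, the collection method or the visit schedule is needed.

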### Study design

This is a phase-4 study of an approved drug, with the aim to delineate additional information for its optimal usage and efficacy. It is designed as a cluster randomised, open-label trial with two study arms, with the ultimate aim of comparing the endpoint results in the intervention versus control arm. A community cluster randomised trial in different settings in Ghana will evaluate the impact and cost-effectiveness of twice-yearly and yearly MDA. The primary outcome is the prevalence of LF. This outcome is selected because it is the prevalence of LF that determines the level of on-going transmission (both parasitological and entomological) and the need to implement Transmission Assessment Surveys and stop MDA [19]. Allocation to study group will be by villages, identified through programme reports, and by disease-control officers in the study districts. The mf prevalence in all communities will be re-evaluated, based on nucleopore filtration of 1 ml of night-blood collected from study participants, prior to assignment to study groups.

The two study groups are:Control group: annual MDA. Clusters (with members aged 5 years and above) will receive 400 μg/kg IVM + 400 mg ALB from trained community drug distributors (CDDs), as part of the ongoing national MDA programmeExpanded frequency group: annual MDA with 400 μg/kg IVM + 400 mg ALB, followed by an additional MDA 6 months later. The drugs will be provided by the national programme and administered by the CDDs, following the structures of the National MDA programme

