**Fig. 2 Fig2:**
[figure not shown]
Standard Protocol Items for Randomised Trials (SPIRIT) Figure – Schedule of enrolments, interventions and assessments

**Table 2 Tab2:** Trial registration data

Data category	Information
Primary registry and trial identification number	ClinicalTrials.gov, ID: NCT03036059
Date of registration in primary registry	26 January 2017
Secondary identifying numbers	Ghana Health Service Ethics Review Committee: 04112/2016 Noguchi Memorial Institute for Medical Research IRB: CPN 062/16-17
Source(s) of monetary or material support	EDCTP grant TMA 2015 CDF - 976
Primary sponsor	Noguchi Memorial Institute for Medical Research
Contact for public queries	[name]
Contact for scientific queries	[name], [name], [name]
Public title	Twice Yearly Treatment for the Control of LF
Scientific title	Cluster Randomised Community-based Trial of Annual Versus Biannual Single-dose Ivermectin Plus Albendazole Against Wuchereria Bancrofti Infection in Human and Mosquito Populations
Country of recruitment	Ghana
Health condition(s) or problem(s) studied	Lymphatic filariasis
Interventions	400 μg/kg ivermectin + 400 mg albendazole tablets given once or twice a year
Key inclusion and exclusion criteria	Inclusion criteria: residency in endemic community for at least 12 months; willingness to provide informed consent/assent; willingness to donate blood (per the protocol) Exclusion criteria: recent residents (<12 months) in the study districts; inability to give informed consent due to illness, serious medical problems or refusal to participate in the study; pregnancy; children below the age of 5 years
Study type	Interventional allocation: randomised Masking: no masking, open label
Date of first enrolment	19 May 2017
Target sample size	1440
Recruitment status	Recruiting
Primary outcome(s)	Change from baseline prevalence of lymphatic filariasis at 12, 24 and 30 months
Key secondary outcome(s)	Longitudinal assessment of transmission dynamics of lymphatic filariasis. Evaluation of community acceptability of twice-yearly treatment. Feasibility of scale-up of twice-yearly treatment

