### Data management and analysis

Field and laboratory data will be recorded by technicians using Samsung Galaxy Tabs A7.0., and entered into a customised database. All data collections tools are coded using CSPro and the data will be transferred onto a secured server.

The analysis will be aimed at (1) assessment of any differences in baseline characteristics between treatment groups, (2) intent-to-treat analysis, i.e. assessment of the effectiveness of the single or twice-yearly treatment regimens on infection intensities and disease outcome and (3) assessment of differences in adherence to the treatment regimens between the groups, potential confounding, and adjusted effectiveness analysis.

All statistical analyses will be based on the clusters with both baseline and endpoint parasitological results. Results will be presented as appropriate effects sizes with a measure of precision (95% CIs). Unadjusted and adjusted results will be presented for all analyses. Covariates in adjusted analyses will be predefined and will include participation in previous MDAs and access and use of bed nets. For continuous outcomes, analyses will adjust for baseline by inclusion of the cluster mean of the outcome in question as a covariate in statistical models.

Demographic and population characteristics of clusters will be compared between study groups. These measures will be tabulated, but no significance tests will be performed to investigate for differences between groups at baseline. Statistical testing will be restricted to comparison between the two community-based treatment groups. Secondary outcomes will be pre-specified for statistical testing along with the primary outcome.

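### The blinding is incomplete: mosquito samples show the village, and so the arm, to staff outside the blind, and nothing protects the statistician's blind once adherence data are opened

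*Protocol article*

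**What the plan says.** **Who is blinded, and how.** The Cluster randomisation section states that "the laboratory technicians conducting the parasitological examinations and the statistician responsible for analysis will be blinded to the group assignment". The means is "using sample/study participant identification codes for samples and results which will not be linked to the study groups". It names no other role, and it does not say that the village is masked.

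**What reveals the arm.** Under Study design, "Allocation to study group will be by villages". Table 2 records "Masking: no masking, open label". The draw is held in front of the communities, "with community leaders invited to select envelopes from the boxes", and fills two boxes "corresponding to the two study groups, each with nine clusters". Table 3 gives treatment yearly for two years in one arm and six-monthly for two years in the other.

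**Mosquito samples.** Under Entomologic surveillance, the catch is "placed in a petri-dish labelled with the village name, GPS coordinates and collection date". Entomologists from the sponsor's institute do the collecting, and the mosquitoes are then identified by morphology. The Analysis strategy under Secondary outcomes adds testing by PCR and LAMP and analysis with pool-screening software. No recoding step is stated between dish and test.

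**The statistician's data.** Data management and analysis lists as its third aim the "assessment of differences in adherence to the treatment regimens between the groups". Survey procedures has the drug distributors keep a register of everyone treated, and Longitudinal surveys uses that register to judge non-compliance. The Analysis strategy also checks geo-referenced residuals for spatial autocorrelation.

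**The concern.** In an open-label trial, masking those who assess samples and analyse data is a main safeguard against assessment bias. Here the masking works by hiding the group label. With whole villages allocated, hiding the label protects only people who also cannot see the village, or who do not know which village is in which arm.

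Two gaps follow. First, entomological indices stand beside parasitological ones in the first detailed objective, yet the people who produce them are not in the blinding statement and their samples name the village. Species identification, pooling and test reading involve some judgement. Second, the statistician is said to be blinded but is due to compare adherence to two regimens that differ in number of rounds. The primary outcome is reported separately at 12, 24 and 30 months, and the ethics bodies review an interim analysis each year. If adherence data are opened at an early time point, the later primary analyses are no longer masked.

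**Working it through.** The plan gives no figure on this point to reproduce. The check is a comparison of the text, with one illustrative calculation.

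**1. Mosquito endpoint (text only).**
- Arm is a function of village (Study design; Cluster randomisation).
- The dish shows the village (Entomologic surveillance).
- The blinding statement covers parasitological examinations and the statistician. Study aims and objectives and Study design treat parasitological and entomological indices as separate things.
- Entomological staff are therefore outside the blind, and the stated label lets them read the arm if they know the allocation.
- The bias cannot be sized. The article gives ten households per community, but neither the number of villages sampled nor an expected mosquito count or infection rate.

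**2. Statistician (text).** Adherence to a regimen is rounds taken out of rounds offered. Over two years the denominators are 2 (annual) and 4 (six-monthly), from Table 3. The comparison therefore needs, or reveals, which group is which.

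**3. Statistician (illustration).** Any record of three or more rounds can come only from the six-monthly arm. Inputs:
- Rounds: at most 2 against 4 (Table 3).
- Completers per community: 58 (Analysis strategy).
- Coverage p: 65% is the programme requirement in the Background. The range 20% to 80% is assumed, because Study population and the Discussion report inaccurate coverage data.
- Rounds and persons are taken as independent.

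Per person, q = P(at least 3 of 4) = 4p³(1−p) + p⁴. At p = 0.65 this is 4 × 0.2746 × 0.35 + 0.1785 = 0.563. Per community, P(at least one such record) = 1 − (1−q)^58.

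| Coverage | q per person | At least one in 58 |
|---|---|---|
| 20% | 0.027 | 0.798 |
| 30% | 0.084 | 0.994 |
| 50% | 0.313 | about 1.00 |
| 65% | 0.563 | about 1.00 |
| 80% | 0.819 | about 1.00 |

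If the nine communities of an arm share one group code, a single such record in any of them decodes it. Even at 20% coverage, the chance of none in all nine is (1 − 0.798)^9 = 0.202^9, below 0.000001.

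Independence of rounds does not drive the result. If the same people took every round, q would equal p, which is larger than the tabulated value at 20%, 30%, 50% and 65% and close to it at 80%.

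**4. At 12 months.** Assume two rounds have been given against one, so that anyone with two rounds reveals the arm and q = p². P(at least one in 58) is 0.906 at 20%, 0.996 at 30%, and about 1.00 at 50% and 65%. The unmasking could therefore happen at the first follow-up.

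**The case against.** The strongest reply is that nothing stated is contradicted.

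- **The dish label breaches no stated blind.** The blinding statement covers parasitological examinations and the statistician, and no masking is claimed for mosquitoes. This stands. The label shows an endpoint left outside the blind.
- **The dish is a field container.** Collectors are in the village anyway, and samples may be recoded before testing under the operating procedures that the article promises. This stands in part. An article need not describe every laboratory step, but this one does fix the label, and it leaves the entomological laboratory staff out of its list of blinded roles.
- **Order of analysis belongs in the analysis plan.** This is fair. The article does not say that adherence data are merged before the primary comparison, which could be run first on coded groups.

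A reader might infer more than the documents support:

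- **That the laboratory blind on the primary outcome fails.** Human samples and results are coded, and nothing shows that the technicians see the village. The article does not say where antigen strips are read, so no argument or figure can rest on that.
- **That the adjusted analysis itself reveals the arm.** The stated covariate is participation in previous rounds. On its natural reading this is history before the trial, which cannot identify the arm. Only the adherence comparison does.
- **That mosquito infection is the main evidence on transmission.** Study design gives that place to the prevalence of infection, and Table 2 lists no mosquito endpoint among its primary or key secondary outcomes.

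**Conclusion.** The blinding is incomplete, in two places.

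1. Staff who identify, pool and test mosquitoes are not in the stated blind, and the prescribed label lets them read the arm. This affects an endpoint in detailed objective 1. It rests on the label, or the information on it, staying with the sample up to testing, and on staff knowing the allocation. The latter is likely in an open-label trial with a public draw. The size of any bias is unknown.
2. The statistician's blind has no stated protection once trial adherence data are opened. Under the assumptions above, decoding is close to certain at any coverage from 20% to 80%. Whether it affects a primary analysis depends on when those data are released, which the article does not say.

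A reader might conclude that the stated blinding cannot hold. That goes too far: the primary comparison can stay masked if it is run before adherence and location data are released. This is a cheap improvement and not a flaw that invalidates the primary result.

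**What to change.** - **Entomologic surveillance:** give each collection a random code before identification, pooling and PCR or LAMP, in place of village name and GPS coordinates. The field coordinator keeps the list linking codes to villages.
- **Cluster randomisation:** extend the blinding statement to the laboratory staff who identify, pool and test mosquitoes.
- **Data management and analysis:** state that the primary comparison at 12, 24 and 30 months is run and locked on dummy group and village codes before treatment-register, adherence and location data go to the statistician. Release after the 12-month lock would unmask the later analyses, so those data should stay with someone other than the analysing statistician until the 30-month comparison is locked.

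The cost is new labels, one linking list kept by existing staff, and a stated order of analysis. The downside is slightly more sample tracking. No visit, sample or participant is added.
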